## Abstract

**Background:**

Oropharyngeal aspiration (OPA) can lead to recurrent respiratory illnesses and chronic lung disease in children. Current clinical feeding evaluations performed by speech pathologists have poor reliability in detecting OPA when compared to radiological procedures such as the modified barium swallow (MBS). Improved ability to diagnose OPA accurately via clinical evaluation potentially reduces reliance on expensive, less readily available radiological procedures. Our study investigates the utility of adding cervical auscultation (CA), a technique of listening to swallowing sounds, in improving the diagnostic accuracy of a clinical evaluation for the detection of OPA.

**Methods:**

We plan an open, unblinded, randomised controlled trial at a paediatric tertiary teaching hospital. Two hundred and sixteen children fulfilling the inclusion criteria will be randomised to one of the two clinical assessment techniques for the clinical detection of OPA: (1) clinical feeding evaluation only (CFE) group or (2) clinical feeding evaluation with cervical auscultation (CFE + CA) group. All children will then undergo an MBS to determine radiologically assessed OPA. The primary outcome is the presence or absence of OPA, as determined on MBS using the Penetration-Aspiration Scale. Our main objective is to determine the sensitivity, specificity, negative and positive predictive values of ‘CFE + CA’ versus ‘CFE’ only compared to MBS-identified OPA.

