### Aims of the study

Our study investigates the utility of cervical auscultation (CA) in the assessment and diagnosis of OPA in children. The primary aim is to determine whether the CFE combined with CA increases the detection of OPA determined by MBS, compared to the CFE only. We hypothesise that the use of CA (compared to not using CA) as an adjunctive clinical tool to assess oropharyngeal dysphagia improves the detection of OPA in children as assessed with the current gold standard, MBS.

Our secondary aim is to determine the perceptual characteristics of common typical respiratory and swallow sound patterns and/or descriptors pre- and post-swallow in children with OPA.

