### Sample size

We plan a sample size of 216 children based on previous research [29] in which the sensitivity of CFE for OPA was 76%. Having 108 children per group provides 80% power (two-sided α = 0.05) to detect a 15% difference between the two groups. A smaller difference between groups was considered insufficient to influence clinical practice. Allowing for 8% attrition (due to unlikely loss to follow-up with both time points at close proximity to each other), a total of 233 children will be enrolled.

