#### Modified Barium Swallow (MBS)

After the clinical evaluation (CFE + CA or CFE), all children will undergo an MBS to objectively define the presence or absence of OPA. The MBS will occur within 2 weeks following the CFE, pending clinical constraints.

During the MBS, swallowing sounds and video recording will be undertaken using the same procedure described above. The MBS will be simultaneously recorded onto a Digital Swallowing Workstation (KayPENTAX, PENTAX Medical Co., USA). A vocal signal will occur at the beginning of all procedures for ease of later synchronising of acoustic and exam data. Our standard clinical protocol is adapted from previous research protocol recommendations for paediatric MBS [3,5,24,44,45].

The presence and severity of OPA will be determined using the Penetration-Aspiration Scale (PAS) [23,46,47]. The PAS describes the severity of penetration of radiology contrast into the airway and the airway response to the penetration using an ordinal 1 to 8 scale, where 1 = no aspiration and 8 = silent aspiration. This scale has high inter- and intra-rater reliability for determining the severity rating of OPA [15,21,23]. PAS scores will be determined for each food and fluid consistency trialed in the MBS. A score of 6, 7 or 8 will be classified as OPA present, while scores of 1, 2, 3, 4 and 5 will be classified as OPA absent.

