### Statistical analyses

Baseline characteristics of the two groups will be presented as means/medians or proportions and their 95% confidence intervals and compared using *t*-tests for normally distributed data, using chi-square tests for proportions and the appropriate non-parametric methods for non-normally distributed data. Baseline demographic and clinical characteristics for those who do and do not withdraw will also be completed. A secondary analysis to re-present the primary results for each of the strata (<1 year and >1 year) will be done to account for the stratification.

For our primary aim, agreement between OPA determined clinical and MBS assessments will be calculated using percent agreement and a kappa coefficient. All evaluable data will be used minus the 8% of dropouts. Taking MBS determination of presence or absence of OPA as the gold standard, sensitivity, specificity, negative predictor value (NPV), positive predictor value (PPV), pretest probability and likelihood ratios will also be calculated. Likelihood ratios will also be calculated.

For our secondary aim, categorical variables of pre-, during and post-swallowing sound parameters will be analysed using a chi-square test to determine which sound qualities are significantly associated with OPA. Multivariate regression analysis will be used to determine whether age, gender, texture, method of intake or clinician level of experience are independent predictors associated with the absence/presence of OPA. All variables will be analysed univariably, then include all those with *p* < 0.15 in a multivariable model. Forward stepwise regression modelling will be employed to identify variables independently associated with OPA and account for interaction effects. The *a priori* statistical level of significance is *p* < 0.05. Missing data points will be coded as a number on the database and analysis completed on the remaining data.

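### The abstract names the MBS reference result as primary outcome, and the protocol does not settle which accuracy measure, compared between arms, decides the hypothesis

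*Protocol article*

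**What the plan says.** - **Primary outcome** (Abstract, Methods): "The primary outcome is the presence or absence of OPA, as determined on MBS using the Penetration-Aspiration Scale".
- **Objective** (same paragraph, next sentence): "Our main objective is to determine the sensitivity, specificity, negative and positive predictive values of" CFE + CA versus CFE alone, judged against MBS.
- **What is randomised** (same paragraph): children are "randomised to one of the two clinical assessment techniques for the clinical detection of OPA". The Clinical Feeding Examination section adds that in the CFE arm the speech pathologist does not wear the headphones.
- **Reference test** (Modified Barium Swallow): after the clinical evaluation, "all children will undergo an MBS to objectively define the presence or absence of OPA". Aims of the study and Statistical analyses both treat MBS as the gold standard.
- **Aim** (Aims of the study): "The primary aim is to determine whether the CFE combined with CA increases the detection of OPA determined by MBS, compared to the CFE only".
- **Sample size**: 108 per group, 80% power, two-sided 0.05, a 15% difference between groups, based on previous research "in which the sensitivity of CFE for OPA was 76" per cent. The Background cites the same reference for 76%, but there it is the agreement of CFE with MBS (against 83% for CFE + CA).
- **Analysis** (Statistical analyses): "For our primary aim, agreement between OPA determined clinical and MBS assessments will be calculated using percent agreement and a kappa coefficient". Sensitivity, specificity, predictive values, pretest probability and likelihood ratios are to be calculated as well.

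**The concern.** A primary outcome in a randomised comparison should be something the allocated technique can affect. Whether a child aspirates on a later MBS is a property of the child. What CA can change is whether the clinician's yes/no judgement matches the MBS. The abstract therefore gives the label of primary outcome to the yardstick and not to the thing being measured.

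Other sections do not settle the matter, because they point to different measures. Sensitivity, agreement and kappa are not interchangeable: agreement can rise through better specificity while sensitivity stays flat, and the reverse. If none of them is fixed as primary, the measure that carries the conclusion can be chosen once the results are known. It is also unclear whether the stated power belongs to the measure that will be reported.

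**Working it through.** **1. The passages side by side**

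| Place | Quantity in the primary role | Between-arm comparison stated? |
|---|---|---|
| Abstract, outcome sentence | OPA on MBS | No |
| Abstract, objective sentence | Sensitivity, specificity, NPV, PPV | Yes, in words (versus) |
| Aims of the study | Detection of OPA | Yes, in words |
| Sample size | A proportion of 76%, called sensitivity | Yes: 15 points, two-sided 0.05 |
| Statistical analyses, primary aim | Percent agreement and kappa | No estimate, interval or test named |

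The Statistical analyses section does name tests elsewhere: *t*-tests and chi-square for baseline, chi-square for the sound parameters, stepwise regression for predictors of OPA.

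**2. Reproducing the sample size**

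Inputs (Sample size section): p1 = 0.76, p2 = 0.76 + 0.15 = 0.91, two-sided α = 0.05 (z = 1.960), power 80% (z = 0.842). Mean proportion = 0.835.

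n = [1.960·√(2·0.835·0.165) + 0.842·√(0.76·0.24 + 0.91·0.09)]² / 0.15²
= [1.960·√0.27555 + 0.842·√0.2643]² / 0.0225 = 94.9, so 95 per arm.

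Continuity correction: n′ = (n/4)·[1 + √(1 + 4/(n·0.15))]² = (94.9/4)·[1 + √1.281]² = 107.9, so **108 per arm**, as stated.

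The trial was thus sized for a two-sided between-arm test of one proportion, with all 108 children in each arm in the denominator.

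**3. Which endpoint has that denominator?**

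*Per-child agreement with MBS (correct or incorrect).* Every child counts. Continuity-corrected power at m per arm = Φ{[0.15 − 1/m − 1.960·√(0.27555/m)] / √(0.2643/m)}. At m = 108 this is 80.1% (84.9% without correction).

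*Sensitivity.* Only MBS-positive children count, so m = 108 × prevalence. The protocol gives no OPA prevalence; the values below are assumptions.

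| Assumed prevalence | MBS-positive per arm | Power, corrected | Power, uncorrected | Total N for 80% (216 / prevalence) |
|---|---|---|---|---|
| 30% | 32.4 | 25% | 37% | 720 |
| 40% | 43.2 | 35% | 47% | 540 |
| 50% | 54.0 | 45% | 56% | 432 |
| 60% | 64.8 | 54% | 64% | 360 |
| 80% | 86.4 | 69% | 76% | 270 |
| 100% | 108 | 80% | 85% | 216 |

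So 216 fits sensitivity at the stated corrected calculation only if every child is MBS-positive.

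**4. Why the two are not interchangeable**

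Agreement = prevalence × sensitivity + (1 − prevalence) × specificity. With specificity unchanged, a 15-point gain in sensitivity raises agreement by 15 × prevalence: 4.5 points at an assumed 30%, 7.5 at 50%, 12 at 80%. A 15-point target on one measure is therefore a different clinical claim from a 15-point target on the other.

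**The case against.** The strongest reply is that the outcome sentence is a loose label in an abstract. The next sentence states the real comparison, the body text already calls MBS the gold standard, and the aims and power statement are plainly two-arm. The choice of test is commonly left to an analysis plan, which is not shown here. The sample size declares no endpoint of its own: its 76% may simply be agreement mislabelled as sensitivity, and then it matches the first measure listed for the primary aim.

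Much of this stands. The intent to compare arms is not in doubt, and the absence of a named test would not by itself be a finding. What remains is misstatement and not omission: the reference result is called the primary outcome, and the sections that could correct this point to different measures. If the 76% is mislabelled, that resolves the conflict in favour of agreement, but the protocol has to say so.

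Three stronger readings are tempting, and the document does not support them.

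- *A test of the primary outcome would reject only about 5% of the time however good CA is.* That would be true of a comparison of MBS-detected OPA between arms, but nothing in the protocol proposes one.
- *The plan only inspects separate within-arm results and so does not test its hypothesis.* The text does not say that the measures are computed by arm, nor that they are judged informally. It says only that they are calculated.
- *Chance imbalance in OPA prevalence would distort kappa by about 0.1.* This needs a specificity and a prevalence that the protocol does not give. At sensitivity 76% and an assumed specificity of 70%, with 108 per arm, a simulated shift of 0.1 or more occurs in about 12% of trials at 10% prevalence, 4% at 20%, 0.4% at 30%, and practically never at 40% or above.

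**Conclusion.** The point holds as a contradiction in what the article fixes. The reference-standard result is named as the primary outcome although the randomised technique cannot be expected to alter it. The measure that decides the hypothesis differs between objective, sample size and analysis. As written, the primary-aim analysis names no between-arm estimate or test; a separate analysis plan may supply one.

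The practical size lies in the power. It is about 80% for 76% versus 91% if the endpoint is per-child agreement. For the same contrast in sensitivity it is 25% to 69% (continuity-corrected) over assumed prevalences of 30% to 80%. The agreement figure uses only the protocol's own inputs and the continuity-corrected formula that reproduces its 108. The sensitivity figures rest also on the assumed prevalence and on equal numbers of MBS-positive children in the two arms. That the technique cannot change the MBS result follows from the design; in an open trial, knowledge of the arm could at most influence how the MBS is scored, which would be bias and not an effect of CA.

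**What to change.** 1. In the abstract, describe OPA on MBS as the reference standard and remove it as primary outcome.
2. Declare one primary endpoint. Per-child correct classification against MBS (percent agreement) keeps 108 per arm at about 80% power for 76% versus 91%. State how results by texture or consistency combine into one result per child. If sensitivity is preferred, restate its power for MBS-positive children only, with the assumed OPA prevalence given.
3. In Sample size, name the 76% consistently with the Background or explain the difference.
4. In Statistical analyses, make the primary analysis the between-arm difference in the chosen proportion, with a 95% CI and a two-sided 0.05 test that accounts for the two age strata.
5. Report the other accuracy measures by arm, and kappa, as secondary.

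The cost is wording. No new data are needed, and if agreement is chosen the sample size is unchanged. If sensitivity is chosen, the restated power may call for a larger trial, or for open acceptance of lower power.

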**Discussion:**

Early detection and appropriate management of OPA is important to prevent chronic pulmonary disease and poor growth in children. As the reliability of CFE to detect OPA is low, a technique that can improve the diagnostic accuracy of the CFE will help minimise consequences to the paediatric respiratory system. Cervical auscultation is a technique that has previously been documented as a clinical adjunct to the CFE; however, no published RCTs addressing the reliability of this technique in children exist. Our study will be the first to establish the utility of CA in assessing and diagnosing OPA risk in young children.

**Trial registration:**

Australia and New Zealand Clinical Trials Register (ANZCTR) number ACTRN12613000589785.

## Background

Feeding difficulties in children encompass a wide spectrum including delayed feeding skills development, disordered sensory processing, preferences for a limited range of food types or textures, aversive feeding behaviours resulting in food refusal and/or difficulty with swallowing (oropharyngeal dysphagia) [1]. Oropharyngeal dysphagia is the term used to define dysphagia involving the oral and/or pharyngeal phases of swallowing. Oropharyngeal dysphagia is clinically important in children as its consequences may include inadequate nutritional intake, dehydration and oropharyngeal aspiration (OPA) [2]. OPA is defined as the entry of fluids, food particles and/or oral secretions into the airway below the level of the true vocal cords [3]. OPA is associated with acute respiratory sequelae such as apnea, tachypnea and pneumonia and chronic sequelae such as chronic cough and bronchiectasis [3,4]. Thus, early detection and appropriate management of OPA is important to prevent chronic pulmonary disease and poor growth in children.

Proving the diagnosis of recurrent OPA as the reason for persistent or chronic respiratory systems remains elusive in respiratory medicine [4]. The first step in evaluating a child for oropharyngeal dysphagia is often a clinical feeding examination (CFE) conducted by a speech pathologist. It is subjective [5,6] but inexpensive, non-invasive, time efficient and repeatable. The CFE involves a case history and mealtime observations of the child’s oral sensorimotor, feeding and swallowing skills [5,7-9]. However, the examination only provides an estimation of the co-ordination and movement of food/fluids through the pharyngeal phase. This is determined through visual observation of laryngeal movement [10], palpation of laryngeal movement [11] and listening to clinical features (e.g. cough [12,13], wet voice [5,14], choking, voice change) [12,14]. In particular, clinical features such as wet voice and wet breathing have been significantly associated with OPA detected on MBS [5]. In children, high sensitivity (92%) on fluids but low sensitivity (33%) on solids for the detection of OPA via CFE has been documented in comparison to MBS findings [12]. Similarly, the CFE in adults is limited by low sensitivity and specificity values for the identification of OPA when compared with MBS [9,15,16]. This limitation to the accurate identification and assessment of OPA means many children require further objective assessment, such as a MBS or fiberoptic endoscopic evaluation of swallowing (FEES), to more accurately detect and identify OPA on a variety of food textures and fluid consistencies.

MBS and FEES have comparable sensitivities [17,18] and reliably detects OPA [15,17,19-22], especially when the Penetration-Aspiration Scale (PAS) is used [21,23]. However, both procedures are usually limited to specialist paediatric tertiary centres, are expensive, and require the expertise of a paediatric speech pathologist and radiologist or an otolaryngologist. These may not be readily available because of scheduling requirements of personnel, suites and equipment. Furthermore, MBS involves radiation although at acceptable levels [24].

### Aims of the study

Our study investigates the utility of cervical auscultation (CA) in the assessment and diagnosis of OPA in children. The primary aim is to determine whether the CFE combined with CA increases the detection of OPA determined by MBS, compared to the CFE only. We hypothesise that the use of CA (compared to not using CA) as an adjunctive clinical tool to assess oropharyngeal dysphagia improves the detection of OPA in children as assessed with the current gold standard, MBS.

Our secondary aim is to determine the perceptual characteristics of common typical respiratory and swallow sound patterns and/or descriptors pre- and post-swallow in children with OPA.

## Methods/Design

### Study design

Open, randomised controlled study. Children randomised to two groups (CFE only vs. CFE + CA) for detection of OPA and compared to that detected on MBS.

### Participants

Inclusion criteria: Children aged < 18 years who are referred for a CFE or MBS at the Royal Children’s Hospital, Brisbane, Australia.

Exclusion criteria: Children deemed medically unfit to complete a CFE and MBS, as determined by the treating medical team. Children can only participate for one series of evaluations.

### Recruitment

The parents/guardians of eligible children will be initially approached by the clinical speech pathologist responsible for the child’s assessment. Parents/guardians interested in participating will then be referred to the principle investigator ([name]). The study will be explained using written information statements and face-to-face interviews. Written informed consent will be obtained from the parents/guardians of children enrolled. Written informed assent will also be obtained from young people aged 12 years and over.

### Randomisation

A computer-generated simple randomisation list, stratified by age (<1 year or ≥1 year), was produced by an external statistician. Allocation concealment will be maintained by group allocation (i.e. CFE or CFE + CA) being concealed in sequentially numbered, opaque envelopes until after consent and baseline information has been obtained. The envelope is opened in front of the treating speech pathologist and caregiver prior to the commencement of their feeding examination.

We stratified by age because swallowing function is influenced by age. The cutoff of 12 months was chosen based on two factors: (1) the swallow-respiration pattern changes at 1 week and between 6 to 12 months of age [34]; (2) anatomical maturity that occurs at approximately 12 months that impacts on a child’s ability to feed more efficiently [35]. These maturity factors include fusion of the mandible halving to improve jaw grading ability, fat pads reducing to increase the oral cavity size and the position of the trachea being more vertical in toddlers than infants.

### Sample size

We plan a sample size of 216 children based on previous research [29] in which the sensitivity of CFE for OPA was 76%. Having 108 children per group provides 80% power (two-sided α = 0.05) to detect a 15% difference between the two groups. A smaller difference between groups was considered insufficient to influence clinical practice. Allowing for 8% attrition (due to unlikely loss to follow-up with both time points at close proximity to each other), a total of 233 children will be enrolled.

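### The 80% power for 108 children per group is attached to sensitivity, but the 76% behind it is reported elsewhere in the article as percent agreement; 108 is enough for agreement and not for sensitivity

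*Protocol article*

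**What the plan says.** All references are to the Protocol article.

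- **Sample size.** The target is set by "We plan a sample size of 216 children based on previous research", in which "the sensitivity of CFE for OPA was 76" per cent. The section continues: "Having 108 children per group provides 80% power" ("two-sided α = 0.05") "to detect a 15% difference between the two groups". Smaller differences are said to be too small to change practice. The number of children expected to be MBS-positive is not mentioned.
- **Background.** The same source is described as finding agreement with MBS of 83% for CFE + CA and 76% for CFE alone. The only sensitivity given from it is 89%, and that is for CFE + CA.
- **Statistical analyses.** For the primary aim, percent agreement and kappa come first. The accuracy measures follow: "Taking MBS determination of presence or absence of OPA as the gold standard, sensitivity, specificity" and the rest are also to be calculated.
- **Participants.** Entry is open to "Children aged < 18 years who are referred for a CFE or MBS", with no requirement that OPA be present.
- **Modified Barium Swallow.** PAS 6 to 8 counts as OPA present and 1 to 5 as absent.

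**The concern.** Sensitivity is a proportion among children who have OPA on MBS. The sample size paragraph names sensitivity as its measure but counts all randomised children. Because specificity and negative predictive value are also objectives, the design itself expects MBS-negative children in each arm, and none of them contributes to sensitivity.

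The label on the 76% also conflicts with the Background, so a reader cannot tell which measure the trial was sized for. This matters because the Abstract lists sensitivity first in the main objective, and the Discussion expects the result to inform whether CA enters routine practice. If sensitivity is believed to carry 80% power and does not, an inconclusive sensitivity comparison could be given more weight than it can bear.

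**Working it through.** **Inputs.** From Sample size: p1 = 0.76, difference d = 0.15 (so p2 = 0.91), two-sided α = 0.05, power 80%, 108 per group. Normal quantiles: 1.960 and 0.842. Mean proportion: 0.835. OPA prevalence π is not in the article and is assumed from 20% to 90%.

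**Step 1: reproduce 108.**

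Uncorrected two-proportion size:

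n = [1.960·√(2·0.835·0.165) + 0.842·√(0.76·0.24 + 0.91·0.09)]² / 0.15²
= (1.0288 + 0.4327)² / 0.0225 = 94.9, i.e. 95 per group.

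With the Fleiss continuity correction:

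n_cc = (n/4)·[1 + √(1 + 4/(n·d))]² = (94.94/4)·[1 + √1.2809]² = 107.9, i.e. **108 per group**.

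This matches the article exactly. So 108 is the number of observations in each denominator.

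**Step 2: which measure has 108 observations per group?**

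- Percent agreement: every evaluable child is an observation, so there are 108. The power claim holds.
- Sensitivity: only MBS-positive children are observations, so there are 108·π. This equals 108 only if every child has OPA, and then specificity could not be estimated.

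**Step 3: power for sensitivity, 76% versus 91%.** With m = 108·π per group:

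power = Φ{[0.15 − 1/m − 1.960·√(0.27555/m)] / √(0.2643/m)}

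The uncorrected version drops 1/m. The constants are 2·0.835·0.165 = 0.27555 and 0.1824 + 0.0819 = 0.2643.

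- Check at m = 108: (0.15 − 0.0093 − 0.0990)/0.0495 = 0.844, giving 80.1%.
- Example at π = 40%, m = 43.2: (0.15 − 0.0231 − 0.1565)/0.0782 = −0.379, giving 35%.

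| Assumed prevalence | MBS-positive per group | Power, corrected | Power, uncorrected |
|---|---|---|---|
| 20% | 21.6 | 14% | 26% |
| 30% | 32.4 | 25% | 37% |
| 40% | 43.2 | 35% | 47% |
| 50% | 54.0 | 45% | 56% |
| 60% | 64.8 | 54% | 64% |
| 70% | 75.6 | 62% | 70% |
| 80% | 86.4 | 69% | 76% |
| 90% | 97.2 | 75% | 81% |

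Rounding m to whole children moves these figures by at most about one point.

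**Step 4: precision and detectable difference at 40% prevalence.** The 95% CI half-width for the sensitivity difference is 1.960·√(0.2643/43.2) = 0.153, about 15 points and so as wide as the target effect. Reaching 80% power from 76% would need CFE + CA sensitivity of about 96% (uncorrected) to 98% (corrected).

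**Step 5: size needed for 108 MBS-positive children per group.** 108/π gives 360 per group (720 in total) at 30%, 270 (540) at 40% and 216 (432) at 50%.

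**The case against.** The best defence is that the trial was sized for percent agreement. The Background calls the 76% agreement, Statistical analyses puts agreement first, and the sample size sentence itself speaks only of a difference between the two groups. On that reading 108 per group is right and the error is one wrong word. This stands, and it is why a reader should not infer outright that the trial's real power is far below 80%: the documents do not establish that sensitivity was the measure intended. The defence does not rescue the paragraph as printed, which calls the figure a sensitivity and so lends 80% power to a measure that does not have it.

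A second defence is that prevalence in a tertiary referral population may be high. The article cannot exclude that, and at 80% to 90% the shortfall is modest. By the method that yields 108, power is still under 80% at any prevalence below 100%; without the correction it reaches 80% at about 90% prevalence.

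A third is that Outcome measures scores OPA per texture, giving several observations per child. Those observations are correlated within a child, and the sample size paragraph counts children, so this does not restore 108 independent positives.

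It is also tempting to say that a null sensitivity result will be read as showing that CA adds nothing. The article does not say so, and it specifies no between-group test of sensitivity. That is a risk to guard against, not a stated plan.

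**Conclusion.** The sample size paragraph is wrong as written on either reading. If agreement was powered, the 76% is mislabelled and the 80% applies to agreement only. If sensitivity was powered, the starting value does not match the article's own account of its source, and the denominator is wrong.

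That 108 counts every child is certain from the arithmetic. How much power sensitivity loses is not: it depends on an OPA prevalence the article does not give. Over 20% to 90% the corrected figure runs from 14% to 75%, taking 76% versus 91% as the sensitivities and 108 evaluable children per group. A large shortfall is a fair description at low to middling prevalence, but not a fact the documents establish.

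**What to change.** First reconcile Background, Sample size and Statistical analyses on which measure was powered. Then rewrite the Sample size paragraph.

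- **If percent agreement:** relabel the 76% as agreement, tie the 80% power to agreement alone, and state that sensitivity is not powered at 80%. Give the expected CI half-width for the sensitivity difference (about 15 points at 40% prevalence).
- **If sensitivity:** replace the 76% with a figure that is a CFE-only sensitivity and cite its source, delete the 80% claim, and state the power and detectable difference for the expected number of MBS-positive children. The pooled MBS-positive rate among children recruited so far can supply the prevalence without comparing the arms.
- **In either case:** state that a non-significant sensitivity difference will be interpreted from its confidence interval and not taken as evidence of no benefit.

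Cost: one paragraph reworded and no additional children. The drawback is a less favourable stated power for sensitivity.

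### The abstract randomises 216 children, but the sample size section needs 216 after attrition and enrols 233; 233 is also two short of the exact allowance

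*Protocol article*

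**What the plan says.** In the protocol article, the Methods paragraph of the abstract states: "Two hundred and sixteen children fulfilling the inclusion criteria will be randomised".

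The Sample size section under Methods/Design uses the same 216 differently. It begins "We plan a sample size of 216 children based on previous research", takes a CFE rate of 76%, and continues "Having 108 children per group provides 80% power (two-sided α = 0.05") "to detect a 15% difference between the two groups". It then adds an allowance, "Allowing for 8% attrition (due to unlikely loss to follow-up with both time points at close proximity to each other"), and ends "a total of 233 children will be enrolled".

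Three other sections fix where the attrition falls:

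- **Randomisation:** the envelope is opened after consent and baseline data, just before the feeding examination.
- **Modified Barium Swallow:** the MBS follows the clinical evaluation, within two weeks where clinical constraints allow.
- **Statistical analyses:** the evaluable data are analysed without the 8% who drop out.

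**The concern.** The same number, 216, has two roles. In the sample size section it is the number that carries the power, before the attrition allowance is added. In the abstract it is the number randomised. The gap of 233 − 216 = 17 children is the whole allowance. A reader who takes the abstract as the plan would conclude that no margin for loss was built in, and that the analysed sample would fall below the 108 per group on which the power statement rests.

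A second, smaller question is whether 233 is itself the right inflation of 216 for 8% loss.

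**Working it through.** **Inputs (Sample size section unless noted).** CFE rate 76%; difference 15 percentage points, read as 76% v 91%; two-sided α = 0.05; power 80%; 108 per group; attrition 8%; enrolment 233. Number randomised in the abstract: 216.

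**1. Reproduce 108 per group.** With p1 = 0.76, p2 = 0.91, mean p̄ = 0.835 and d = 0.15:

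- n′ = [1.96·√(2·p̄(1−p̄)) + 0.8416·√(p1(1−p1) + p2(1−p2))]² / d²
- n′ = [1.96·√0.27555 + 0.8416·√0.2643]² / 0.0225 = 94.9 per group, without correction
- With continuity correction: n = (n′/4)·[1 + √(1 + 4/(n′d))]² = 107.9, so 108 per group and 216 in total.

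The corrected version gives the plan's figure exactly; the uncorrected one gives 95. The article names no formula, so the correction is inferred from this match.

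**2. Reproduce 233.** 216 × 1.08 = 233.28, printed as 233. If 8% of those enrolled are lost, the number needed to keep 216 is 216/0.92 = 234.8, so 235. For equal arms, 108/0.92 = 117.4, so 118 per arm or 236.

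**3. Number left after 8% loss.**

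- 233 enrolled: 233 × 0.92 = 214.4, about 107 per group
- 216 randomised: 216 × 0.92 = 198.7, about 99 per group

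**4. Power at each size.** Uncorrected power is Φ{[d√n − 1.96·√0.27555] / √0.2643}. The corrected version, obtained by inverting the formula in step 1, subtracts a further 1/√n in the numerator.

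| Evaluable per group | Corrected | Uncorrected |
|---|---|---|
| 108 (target) | 80.1% | 84.9% |
| 107.2 (233 enrolled, 8% lost) | 79.7% | 84.6% |
| 99.4 (216 randomised, 8% lost) | 76.2% | 81.8% |

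With whole numbers of 107 and 99 per group, the corrected values are 79.6% and 76.0%.

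**5. Can the two totals be reconciled?** One could read 233 as children consented and 216 as children randomised, with the 8% lost in between. The text does not allow this. The sample size section attributes the loss to follow-up between two closely spaced time points, and these are the clinical evaluation and the MBS. Allocation is revealed before the first of them, so the loss comes after randomisation. The analysis section also removes the dropouts from the data to be analysed. The 216 in the abstract is therefore best read as the evaluable target given as the number randomised.

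**The case against.** The case for leaving this alone has four parts.

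**The inflation slip is negligible.** It is two children, under 1% of the total, and 79.7% rounds to the stated 80%. The 8% is itself a forecast. The article describes simple randomisation within age strata and mentions no blocking, so arm sizes vary by chance anyway: with 233 children, the standard deviation of one arm under simple randomisation is √233/2 = 7.6. This stands. A reader might infer that the 80% power claim fails at 233, but a shortfall of 0.3 to 0.5 points does not support that.

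**The methods section governs.** It states 233 and gives the reason, so the allowance is in the plan and the abstract only repeats a headline figure. This largely stands. A reader might infer that recruitment would end at 216, but the article states no such stopping rule, and Trial status gives only a planned two-year period. The loss of power at 216 is therefore conditional. The objection does not remove the contradiction, because the abstract uses the word for randomisation and not for evaluable children.

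**The power loss depends on an unstated formula.** This stands. Without continuity correction, power remains above 80% even at 99 per group. That formula gives 95 per group, however, so it is not the one that yields 108. Both ends of the range should be shown.

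**The input rate is less certain than the slip.** The Background reports the 76% from the same reference as agreement with MBS, whereas the sample size section calls it sensitivity. This limits how much weight a fraction of a power point can bear. It does not affect the conflict between 216 and 233.

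**Conclusion.** The point holds as a conflict between two current statements of a key design figure: 216 randomised in the abstract, and 216 needed after attrition with 233 enrolled in the sample size section. If the abstract were followed, about 199 children would be evaluable and power would be about 76% on the formula that reproduces 108 per group, or about 82% uncorrected. Nothing in the article shows that the abstract's number would be the one followed.

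The inflation by multiplication is a minor, rounding-level slip: 233 instead of 235, about 214 evaluable instead of 216, and power of about 79.7%.

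These figures assume 76% v 91%, equal arms, exactly 8% loss after randomisation, and the plan's own use of all children in each group as the denominator. Whether that denominator suits a comparison of sensitivities is a separate matter and is not judged here.

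**What to change.** In the abstract, describe 216 as the target number of evaluable children and give the same number randomised as the sample size section. For that number, choose one of two:

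- keep 233, and state that 8% loss leaves about 214 evaluable (107 per group) with just under 80% power on the plan's basis; or
- state 235, from 216/0.92, or 236 if equal arms of 118 are wanted.

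Naming the sample size formula, including whether a continuity correction was used, would let readers reproduce 108 directly.

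The first option costs only wording. The second adds two or three children. Neither changes the design or the analysis.
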